### 8.3.2 DEFINITION OF SERIOUS ADVERSE EVENTS (SAE)

An adverse event (AE) or suspected adverse reaction is considered "serious" if, in the view of the investigator/sponsor, it results in any of the following outcomes: death, a life-threatening adverse event, inpatient hospitalization or prolongation of existing hospitalization, a persistent or significant incapacity or substantial disruption of the ability to conduct normal life functions, or a congenital anomaly/birth defect. Important medical events that may not result in death, be life-threatening, or require hospitalization may be considered serious when, based upon appropriate medical judgment, they may jeopardize the participant and may require medical or surgical intervention to prevent one of the outcomes listed in this definition. Examples of such medical events include allergic bronchospasm requiring intensive treatment in an emergency room or at home, blood dyscrasias or convulsions that do not result in inpatient hospitalization, or the development of drug dependency or drug abuse.

---

### 8.3.3 CLASSIFICATION OF AN ADVERSE EVENT

---

#### 8.3.3.1 SEVERITY OF EVENT

The Investigator will determine the severity of each AE using the most current version of the Common Terminology Criteria for Adverse Events (CTCAE). Adverse events that do not have a corresponding CTCAE term will be assessed according to the following guidelines:

- **Mild** – Events require minimal or no treatment and do not interfere with the participant's daily activities.
- **Moderate** – Events result in a low level of inconvenience or concern with the therapeutic measures. Moderate events may cause some interference with functioning.
- **Severe** – Events interrupt a participant's usual daily activity and may require systemic drug therapy or other treatment. Severe events are usually potentially life-threatening or incapacitating. Of note, the term "severe" does not necessarily equate to "serious".

---

#### 8.3.3.2 RELATIONSHIP TO STUDY INTERVENTION

All adverse events (AEs) must have their relationship to study intervention assessed by the investigator based on temporal relationship and his/her clinical judgment. The degree of certainty about causality will be graded using the categories below. In a clinical trial, the study product must always be suspect.

- **Definitely Related** – There is clear evidence to suggest a causal relationship, and other possible contributing factors can be ruled out. The clinical event, including an abnormal laboratory test result, occurs in a plausible time relationship to study intervention administration and cannot be explained by concurrent disease or other drugs or chemicals. The response to withdrawal of the study intervention (dechallenge) should be clinically plausible. The event must be pharmacologically or phenomenologically definitive, with use of a satisfactory rechallenge procedure if necessary.
- **Probably Related** – There is evidence to suggest a causal relationship, and the influence of other factors is unlikely. The clinical event, including an abnormal laboratory test result, occurs within a reasonable time after administration of the study intervention, is unlikely to be attributed to concurrent disease or other drugs or chemicals, and follows a clinically reasonable response on withdrawal (dechallenge). Rechallenge information is not required to fulfill this definition.
- **Potentially Related** – There is some evidence to suggest a causal relationship (e.g., the event occurred within a reasonable time after administration of the trial medication). However, other factors may have contributed to the event (e.g., the participant's clinical condition, other concomitant events). Although an AE may rate only as "possibly related" soon after discovery, it can be flagged as requiring more information and later be upgraded to "probably related" or "definitely related", as appropriate.
- **Unlikely to be related** – A clinical event, including an abnormal laboratory test result, whose temporal relationship to study intervention administration makes a causal relationship improbable (e.g., the event did not occur within a reasonable time after administration of the study intervention) and in which other drugs or chemicals or underlying disease provides plausible explanations (e.g., the participant's clinical condition, other concomitant treatments).
- **Not Related** – The AE is completely independent of study intervention administration, and/or evidence exists that the event is definitely related to another etiology. There must be an alternative, definitive etiology documented by the clinician.

#### 8.3.3.3 EXPECTEDNESS

The PI will be responsible for determining whether an adverse event (AE) is expected or unexpected. An AE will be considered unexpected if the nature, severity, or frequency of the event is not consistent with the risk information previously described for the study intervention.

#### 8.3.4 TIME PERIOD AND FREQUENCY FOR EVENT ASSESSMENT AND FOLLOW-UP

The occurrence of an adverse event (AE) or serious adverse event (SAE) may come to the attention of study personnel during study visits or phone contacts with a study participant. Assessments for AE will occur as outlined in the Schedule of Activities (**Section 1.3**).

All AEs including local and systemic reactions not meeting the criteria for SAEs will be captured on the appropriate case report form (CRF). Information to be collected includes event description, time of onset, clinician's assessment of severity, relationship to study product (assessed only by those with the training and authority to make a diagnosis), and time of resolution/stabilization of the event. All AEs occurring while on study must be documented appropriately regardless of relationship. All AEs will be

followed until the event has resolved or any permanent sequelae are stable. The study team will work with the local clinicians to determine the characterization and severity of an AE and the proper course of treatment, if appropriate.

Any medical condition that is present at the time that the participant is screened will be considered as baseline and not reported as an AE. However, if the study participant's condition deteriorates at any time during the study, it will be recorded as an AE.

Changes in the severity of an AE will be documented to allow an assessment of the duration of the event at each level of severity to be performed. AEs characterized as intermittent require documentation of onset and duration of each episode.

The study coordinator, with supervision of the PI, will record all reportable events with start dates occurring any time after informed consent is obtained until 7 (for non-serious AEs) or 30 days (for SAEs) after the last day of study participation. At each study visit, the investigator will inquire about the occurrence of AE/SAEs since the last visit. Events will be followed for outcome information until resolution or stabilization. For events that are not resolved or stable at the last study visit, the study team will continue to contact the family by phone on a weekly basis until resolution or stabilization.

---

#### 8.3.5 ADVERSE EVENT REPORTING

Subjects will be encouraged to notify the study team immediately should any adverse event occur. Formal review of adverse events will occur at each visit and telephone call as detailed in the Schedule of Activities (**Section 1.3**). The PI or a qualified co-investigator will review all adverse events within 48 hours and serious adverse events within 24 hours of becoming aware of the event or as soon as possible if clinical treatment or dose reduction may be necessary. An adverse event log will be maintained. Reports of all AEs will be provided to the DSMB after completion of Visit Day 1 for the first 5 subjects and then after completion of the Day 1 Visits for each additional 10 subjects (i.e. after subjects 15, 25, and 35, etc...) or every 6 months, whichever is sooner. The study team will comply with all local legal, regulatory, and IRB requirements with regards to adverse events.

---

#### 8.3.6 SERIOUS ADVERSE EVENT REPORTING

All study personnel will immediately report to the sponsor investigator any serious adverse event (SAE), whether or not considered study intervention related, including those listed in the protocol or investigator brochure and must include an assessment of whether there is a reasonable possibility that the study intervention caused the event. The PI will report all SAEs to BioMarin within 24 hours of being made aware of an occurrence using FDA form 3011A.

All SAEs will be followed until satisfactory resolution or until the PI deems the event to be chronic or the participant is stable.

The study sponsor/PI will be responsible for notifying the Food and Drug Administration (FDA) of any unexpected fatal or life-threatening suspected adverse reaction as soon as possible, but in no case later than 7 calendar days after the sponsor's initial receipt of the information. In addition, the sponsor investigator must notify FDA and BioMarin must notify all participating investigators in an Investigational New Drug (IND) safety report of potential serious risks, from clinical trials or any other source, as soon as possible, but in no case later than 15 calendar days after the sponsor investigator determines that the information qualifies for reporting. The IND safety report will be submitted to the FDA and to BioMarin

using Form 3500A as per FDA regulations and will follow the appropriate FDA guidance (see <https://www.fda.gov/drugs/investigational-new-drug-ind-application/ind-application-reporting-safety-reports>).

All reports to BioMarin will be address to BioMarin's Drug Safety Department is as follows:

BioMarin Pharmaceutical Inc.  
[name]  
[name]  
[contact]  
[contact]  
Email: [[contact]](mailto:[contact])

---

#### 8.3.7 REPORTING EVENTS TO PARTICIPANTS

AEs or SAEs will be reported to all participants via email and mail if either the IRB determines that this information changes the risk benefit considerations for the trial or if reporting is mandated by the DSMB. An amendment will be submitted to the IRB containing the relevant new information and any applicable informed consent updates.

---

#### 8.3.8 EVENTS OF SPECIAL INTEREST

Not applicable

---

#### 8.3.9 REPORTING OF PREGNANCY

Not applicable

---

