|---------------------------------------------------------------------------------------------------------------------------------------------------------------------------------------------------------------------------------------------------------------------------|-----------|-----------------------------------------------------------------------------------------------------------------------------------------------------------------------------------------------------------|
| 
 
To explore the relationship between genetic etiology and safety and efficacy
 
To evaluate changes from baseline in quality of life using the QoLISSY scale after 12 months of daily SC injections of vosoritide
 
 |           | 
in achondroplasia patients.
 
Vosoritide antibody assessment is a standard safety metric.
 
QoLISSY is a validated scale for quality of life measurement in children with short stature.
 |

During the extension study, all of the primary, secondary and exploratory aims and endpoints will remain the same, but the timeframe will be extended from 12 months until growth cessation or subject withdrawal from the study.

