### 5 STUDY POPULATION

#### 5.1 INCLUSION CRITERIA

Inclusion and exclusion criteria will be pre-screened based on information provided by the referring clinician. All inclusion and exclusion criteria will then be verified at the screening visit and official screening laboratory studies will be performed as part of that visit. There will be no birth weight or length inclusion or exclusion criteria.

In order to be eligible to participate in this study, an individual must meet all of the following criteria:

1. Parent(s) or guardian(s) are willing and able to provide written, signed informed consent after the nature of the study has been explained and prior to performance of any research-related procedure. Also, subjects under the age of 18 are willing and able to provide assent (if required) after the nature of the study has been explained and prior to performance of any research-related procedure.
2. Stated willingness to comply with all study procedures and availability for the duration of the study
3. Age  $\geq 3$  years 0 days AND  $\leq 10$  years 364 days for males,  $\leq 9$  years 364 days for females
4. Pre-pubertal defined as Tanner Stage 1 breasts in females and testicular volumes  $\leq 3$  cc in males. This must be confirmed at the Day 1 visit prior to initiation of vosoritide.
5. Patient height  $\leq -2.25$  SDS. All height SDS values are calculated using the CDC growth charts/data tables.

6. Patients with pathogenic or likely pathogenic variants in genes known to cause the specific genetic subgroups of short stature listed below are eligible for inclusion in the study. Pathogenicity of variants will be classified as per the American College of Medical Genetics criteria with the exception of *ACAN* mutations as detailed below. Documentation of the presence of the variant must be obtained using a lab results report from a CLIA certified laboratory. Classification of the variant's pathogenicity status will be performed by the Children's National study team.
- A. CNP deficiency due to mutations in *NPPC* – Subjects with heterozygous or homozygous defects in *NPPC* are eligible.
  - B. Hypochondroplasia – Subjects with heterozygous variants in *FGFR3* gene associated with hypochondroplasia are eligible. Subjects with variants in *FGFR3* known to cause achondroplasia or thanatophoric dysplasia or SADDAN syndrome will be excluded.

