  - For subjects with hypochondroplasia or *ACAN* mutations – A positive response is defined as an increase in annualized growth velocity of 1.6 cm/year when comparing 6-month observation period to initial 12 months of vosoritide treatment. This criterion is based on the adjusted mean response of patients with achondroplasia in the Phase III trial of

vosoritide which is a clinically significant response. ACAN patients can also have disproportion and are included in this category.

- For subjects with Rasopathies, *SHOX* mutations, *NPR2* mutations or *CNP* deficiency - A positive response is defined as an increase in annualized growth velocity of 3 cm/year when comparing 6-month observation period to initial 12 months of vosoritide treatment. This higher response criterion is due to growth hormone being approved for *SHOX* deficiency, Noonan syndrome, and for idiopathic short stature which could encompass *NPR2* mutations and *CNP* deficiency. In these types of patients, an increase in annualized growth velocity of 3 cm/year is more typical for patients treated with growth hormone, and thus, we want to ensure that patients treated with vosoritide have a similarly favorable response. However, if a subject has previously been treated with growth hormone and it was discontinued due to a poor response, if the increase in annualized growth velocity on vosoritide is greater than it was for growth hormone but still less than 3 cm/year, the subject can continue on vosoritide in the extension phase.
- 4. There are no inclusion criteria based on height or pubertal status for the extension phase of the protocol. Subjects may continue into the extension phase regardless of their height or pubertal status as the 12 Month Visit.

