#### Extension Phase Exclusion Criteria:

At the 12 Month Visit, the subject's bone age via the Greulich and Pyle method will not be greater than or equal to 13 years in females and 15 years in males. These patients have limited remaining growth potential.

None of the other exclusion criteria will be applied to the extension phase of the study as they would have been dealt with as adverse events during the trial.

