#### 6.1.2 DOSING AND ADMINISTRATION

During the study, vosoritide will be administered as a single 15  $\mu\text{g}/\text{kg}$  subcutaneous injection given daily at approximately the same time each day whenever possible. The time of day of administration will be up to the individual subject and their guardian. It will be given 7 days per

week. The same injection site should not be used 2 days in a row, and sites should be rotated. Doses may be administered in any of the common subcutaneous areas (upper arm, thigh, abdomen, buttocks). If a dose is missed and noticed within 12 hours of the missed dose, it should be given at that time. If it has been more than 12 hours since the time of the missed dose, that dose should be skipped and the regular dose should be given the following day.

Vosoritide will be given for an initial 12-month period followed by an extension phase until cessation of growth or subject withdrawal from the study or until vosoritide becomes commercially available for the subject's indication. Doses will be given in the clinic during the Day 1, Day 2, 6 Month and 12 Month Visits prior to pharmacokinetic sampling. At the 6 month visit, the subject will be weighed. The dose of medication will be recalculated using the same 15 µg/kg dose but adjusted for the new weight. There will be no other dose increases in the protocol. After consultation with the DSMB, the dose may be reduced by 20% if the subject meets the individual stopping criteria on one occasion as detailed in **Section 7.1** below.

Subjects with a good response at 12 months will be offered participation in the extension phase of the study. A good response is defined in the inclusion criteria above. Subjects in the extension phase will continue to be seen in-person every 6 months at Children's National with telephone visits at the 3-month time point mid-way between in-person visits.

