#### Individual Subject Stopping Criteria

Dosing for the subject will be temporarily discontinued and DSMB will be informed (at a minimum) if any of the following occur:

- Any treatment emergent adverse event (TEAE) at least Grade 3 (according to the most current version of the CTCAE) assessed by the PI determined to be related to the study drug
- Any two TEAEs Grade 2 experienced by the same subject within one week (according to the CTCAE) including 2 symptomatic hypotension events within one week (non-urgent medical intervention indicated) or any Grade 3 hypotension event (medical intervention or hospitalization indicated) assessed by the PI. Two grade 2 injection site reactions such as presence of swelling at the injection site will not require urgent reporting to the DSMB or subject suspension as long as no further intervention was required.
- Prolongation of QTcF (QT corrected Fredericia) interval to more than 500 msec, ventricular tachycardia greater than five beats
- Any clinically significant worsening of existing disproportionate growth, as determined by physical measurement ratios and/or PI assessment based on measurement or clinical observation findings
  - o Sitting height to standing height ratio – Worsening of ratio of more than 1 standard deviation from initiation of therapy based on NHANES data .
  - o Arm span minus height – Worsening of more than 1 standard deviation since initiation of therapy with a SDS either >+2 or <-2. Data is based on Gerver et al.
- Excessively rapid increase in growth velocity (defined as greater than the 90th percentile on age- and gender-specific growth charts) sustained over a period of 2 years or associated with an adverse event such as joint pains or deformity 
- Clinically significant worsening of scoliosis as observed via clinical or radiographic assessment. This is defined as a new onset asymmetry noticed during a forward bend test or an increase in Cobb angle of >10 degrees from baseline or any Cobb angle of >20 degrees at any point in the study.

Subjects may continue in the extension phase of the study until achieving near final adult height which will be defined as either:

- A growth velocity <1.5 cm/year over the prior 12 months
- A bone age via the Greulich and Pyle method of 13 years in females and 15 years in males.

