## 7.2 PARTICIPANT DISCONTINUATION/WITHDRAWAL FROM THE STUDY

Subjects (or their legally authorized representative) have the right to withdraw their consent to participate in the study at any time without prejudice. The Investigator must withdraw from the study any subject who requests to be withdrawn. A subject's participation in the study may be discontinued at any time at the discretion of the Investigator and in accordance with his/her clinical judgment. When possible, the tests and evaluations listed for the termination visit should be carried out.

Reasons for which a subject may be withdrawn from the study or from study treatment by the Investigator include but are not limited to the following:

- Subject experiences a serious or intolerable AE
- Subject develops a clinically significant laboratory abnormality
- Subject requires medication or medical procedure prohibited by the protocol
- Subject does not adhere to study requirements specified in the protocol
- Subject was erroneously admitted into the study or does not meet entry criteria
- Subject is lost to follow-up

Subjects may continue in the extension phase of the study until achieving near final adult height which will be defined as either:

- A growth velocity <1.5 cm/year over the prior 12 months

- A bone age via the Greulich and Pyle method of 13 years in females and 15 years in males.

Non-adherence to study medication administration will be monitored via review of the medication administration log and counting of empty vials at the 6 and 12 month visits. Subjects will be encouraged to have 100% compliance with study drug administration. If during a 30 day period, a subject misses 5 or more shots, they will be considered non-compliant with the study protocol. They will be given a warning that compliance must improve or they will be withdrawn from the study. If there is a second 30 day period when the subject misses 5 or more shots, they will be withdrawn from the study.

The reason for participant discontinuation or withdrawal from the study will be recorded on the Termination Visit Case Report Form. Subjects who sign the informed consent form but do not receive vosoritide may be replaced. Subjects who sign the informed consent form, and receive vosoritide, and subsequently withdraw, or are withdrawn or discontinued from the study will not be replaced.

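### Section 8.3.9 rules out pregnancy reporting for the whole protocol, which fits the pre-pubertal first 18 months but not the extension, where girls are dosed whatever their pubertal status

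*Protocol*

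**What the plan says.** Section 8.3.9, headed "8.3.9 REPORTING OF PREGNANCY", contains only the entry Not applicable. It is not restricted to a phase, and the extension has no safety-reporting section of its own.

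The two phases take different populations:

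- **Initial phase (5.1, item 4).** Subjects must be pre-pubertal. "This must be confirmed at the Day 1 visit prior to initiation of vosoritide".
- **Extension (5.1, extension item 4).** "Subjects may continue into the extension phase regardless of their height or pubertal status".

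Extension dosing runs "until cessation of growth or subject withdrawal from the study or until vosoritide becomes commercially available" for the subject's indication (6.1.2). Sections 7.1 and 7.2 set the growth endpoint as either a velocity below 1.5 cm/year over the preceding 12 months or "A bone age via the Greulich and Pyle method of 13 years in females and 15 years in males". The same bone ages bar entry to the extension (5.2). Bone age is read every 12 months (1.2 and 8.2).

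Safety and tolerability is a primary objective, and section 3 carries it forward: "During the extension study, all of the primary, secondary and exploratory aims and endpoints will remain the same".

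**The concern.** The entry in 8.3.9 suits a study of pre-pubertal children followed for 18 months. The amendment history shows that the extension was added in version 2.6, so the entry probably predates it. The extension expects participants to mature: Tanner stage is recorded at each in-person visit, and written assent is sought from age 12. For these girls the one section that names pregnancy says that the subject does not arise.

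If a participant became pregnant on vosoritide, three things would matter: a prompt report, a decision about dosing, and a known outcome. As written, each depends on how individual staff read general clauses, in a phase where safety is still a primary aim.

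**Working it through.** The plan gives no figure to reproduce. The check has two parts: whether the extension can reach girls for whom pregnancy is conceivable, and what the other safety clauses would do.

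**1. Ages in the extension (girls)**

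Inputs: screening age from 3 years 0 days to 9 years 364 days (5.1); 6 months of observation, then 12 months of treatment; Day 1 and Month 12 windows of 2 weeks each (1.3); bone age stop at 13, read yearly.

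Age at extension entry = screening age + 0.5 + 1.0 years.

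- Youngest: 3.0 + 1.5 = 4.5 years.
- Oldest: just under 10.0 + 1.5 = about 11.5 years. The windows total 4 weeks, or 0.08 years, giving 11.4 to 11.6.

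Let d be bone age minus chronological age, and assume that bone age advances one year per year. Both d and this rate are assumptions; the protocol gives neither. Bone age 13 is reached at age 13 − d. A yearly reading can add up to one year, so dosing stops between 13 − d and 14 − d.

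| d (years) | Age at stop | Oldest girl: bone age at yearly readings from age 12.5 | Her extension dosing |
|---|---|---|---|
| +1 | 12 to 13 | 13.5 at age 12.5 | 1.0 year |
| 0 | 13 to 14 | 12.5, then 13.5 at age 13.5 | 2.0 years |
| −1 | 14 to 15 | 11.5, 12.5, then 13.5 at age 14.5 | 3.0 years |

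A girl enrolled at 3 stops within the same age ranges. The velocity rule, withdrawal or commercial availability can end dosing sooner. The bone-age cap therefore narrows the window without closing it.

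**2. What the other clauses would do with an uncomplicated pregnancy**

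- **7.1, opening paragraph.** A new finding of clinical relevance is to be reported as an adverse event, and the investigator decides whether management should change. This could take in a pregnancy, although it is not named.
- **8.3.4, 8.3.5 and 10.1.6.** Once classed as an adverse event, it is reviewed by the principal investigator or a co-investigator within 48 hours, reported to the DSMB at least every 6 months, and followed until resolved or stable.
- **8.3.1.** A reportable adverse event must be untoward. An uncomplicated pregnancy is not clearly that.
- **8.3.2 and 8.3.6.** Hospitalization, a congenital anomaly or an important medical event is serious and goes to the funder within 24 hours. An uncomplicated pregnancy meets none of these except by judgement.
- **8.2, health events.** A change in health status is recorded on a case report form. Nothing further is required unless it is classed as an adverse event.
- **7.1 stopping criteria and 7.2 withdrawal reasons.** Pregnancy is in neither list. Under 7.2, "participation in the study may be discontinued at any time at the discretion of the Investigator", which permits action without requiring it.

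Taken together, capture, DSMB reporting and follow-up are available by interpretation. A 24-hour report to the funder and a defined dosing action are not required.

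**The case against.** The strongest reply is that 7.1 already closes the gap. A pregnancy in a dosed girl of 12 to 15 is hard to see as anything but clinically relevant, so it would be reported as an adverse event, reviewed within 48 hours, shown to the DSMB and followed. A template heading marked Not applicable does not cancel mandatory wording elsewhere.

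Much of this stands. A reader might infer from 8.3.9 that a pregnancy would go unrecorded or never reach the DSMB; 7.1, 8.3.4, 8.3.5 and 10.1.6 do not support that. What the reply leaves open is that the route depends on reading an unnamed event into a general clause, while the section that does name it says reporting does not apply. Even on that route, DSMB reports may be up to 6 months apart, the 24-hour line to the funder is not triggered, and the dosing decision is unspecified.

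Two further objections limit the size of the point. The years in the table are years of dosing, not years at risk of pregnancy; the protocol gives nothing on menarche or fertility below bone age 13, and the number affected could be zero. And none of the text available for this point describes a fetal risk. Section 2.3.1 and the consent documents were not part of it, so a mandatory permanent stop cannot be argued from what is shown.

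**Conclusion.** The entry in 8.3.9 is right for the initial 18 months and wrong for the extension. The defect is limited: pregnancy is not named anywhere in the operative safety rules, no prompt report to the funder is required when it is uncomplicated, and no dosing action is fixed.

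The number at risk is not stated. It is probably small and is below the 75 who may enrol, because it is confined to girls who met the 1.6 or 3 cm/year response rule (or its growth-hormone exception) and had a bone age under 13 at extension entry. The stopping ages of 12 to 15 rest on the assumed range of one year either side for bone age and on its advancing one year per year.

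Two stronger readings should be avoided. The synopsis mentions participation to about age 18, from which a reader might infer dosing of girls to that age. With the female cap of 13 and a yearly reading, stopping at 18 would need 13 − d ≤ 18 ≤ 14 − d, a bone age 4 to 5 years behind. Nor does the point touch the efficacy findings: the 12-month results are unaffected.

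**What to change.** 1. In 8.3.9, limit Not applicable to the initial 18 months.
2. For the extension, require any known participant pregnancy to be reported on the 24-hour line of 8.3.6, notified to the DSMB, and followed to outcome.
3. In 7.1, add pregnancy to the individual criteria under which dosing is held and the DSMB informed. A hold with DSMB consultation matches the existing mechanism and goes no further than the visible text supports.

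The cost is a short amendment, an update to the extension consent addendum and one case report form page. It adds no patients, scheduled visits or scheduled tests. The extension laboratory panel lists no pregnancy test, so detection would rest on disclosure or routine clinical care; scheduled testing would be a separate decision with its own cost.
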